### 2.7. Study Procedures

At the screening visit (SV), Day 0, patients will be provided with an informed consent procedure and documentation of the informed consent discussion. The IRB-approved informed consent is obtained prior to performing any trial-related procedures. Once consent is obtained, the physician will document the onset of the ulcer per medical record or patient report, with preference to documentation over self-reporting. The patient’s medical history and demographic information will be recorded. For female patients of childbearing potential, urine or blood pregnancy tests will be conducted. A physical examination will follow and is focused on the integumentary system. Next, a Fitzpatrick score will be assigned. The Fitzpatrick score is a validated assessment of skin tones meant to increase enrollment of minority populations in clinical trials. This is necessary, as an objective assessment of skin color is recommended in all clinical trials, and when using optical diagnostics, the color of the skin is important data.

Due to the inaccuracy of length times width measurements using a hand-held ruler, wound surface area measurement will be assessed using digital planimetry. There are several systems commercially available that accurately measure wound surface area. In this trial, the MolecuLight device in standard photographic mode will provide accurate planimetry. Finally, the patient will complete a baseline pain assessment using a visual analog or numeric scale. Prior or concomitant medications will be reviewed. Quality of life questionnaires will not be used in this trial design due to the short duration of the trial.

This trial design does not incorporate a run-in period such as those used for advanced wound care modalities (e.g., cellular and tissue-based products for wound care (CTP). The goal of antiseptic trials is to identify products that reduce the level of bacteria in the wound; therefore, a run-in to assess healing rate prior to enrollment is unnecessary.

All consenting subjects meeting eligibility requirements will be immediately moved to treatment visit (TV) 1. Subjects will be seen by the principal investigator (PI) or designee on TV 1. After the first visit, the PI will prescribe the frequency of wound cleansing following the randomization scheme. In this trial, patients will be stratified by site and randomized using a block randomization scheme. Typically, a block randomization of four is used, with occasional blocks of two or six to prevent provider bias. Patients are randomized to either the treatment or control group using a 1:1 ratio. There are several commercially available automated systems that provide randomization services. They are convenient but add cost to the trial. The patient, PI, and study staff will remain blinded to the allocation.

Subjects will be seen weekly for a period of 28 days, +/−3, for a total of 5 visits. Table 1 details the schedule of events for the study.

The MolecuLight Procedure (MiX) will be completed using the MolecuLight i:X Imaging Device, a handheld point-of-care medical device comprised of a high-resolution color LCD display and a touch-sensitive screen with integrated optical and microelectronic components. MolecuLight i:X detects bacteria at levels greater than >10^4^ CFU/g [9]. The MiX procedure will be performed before and after wound cleansing for accurate point-of-care digital assessment of bacterial load on the target ulcer to aid the primary investigator or designee in the most precise wound bed preparation and monitoring of wound healing.

Following TV 5 or upon early termination for any reason, a study exit form will be completed along with placement of SOC dressings if the target ulcer is not healed.

Enrolled patients who meet the inclusion criteria and have provided consent will be randomized 1:1 to have their wound cleansed with either NSS-HG or AMC-AMG. Unblinded staff will prepare labeled solutions of the two treatments that are consistent with the randomization scheme. Unblinded staff will also provide the patient with a four-week supply of their assigned treatment.

After the screening visit, enrolled patients will start treatment visit 1. At this treatment visit, initial procedures will be conducted:Confirmation of inclusion criteria and randomization to treatment;Photography of the wound and digital surface area measurement;Fluorescence imaging;Wound cleansing with randomly assigned treatment;Post debridement fluorescence imaging;Swab of wound for protease activity;Application of wound dressing at the discretion of the principle investigator;A four-week supply of the assigned treatment is provided to patients;If applicable, wound debridement, measurement, off-loading walker fitting (DFU applicable), or application of multilayer compression (VLU) is conducted.

At the subsequent treatment visits (visits two through four), all steps will be repeated except for step eight. At the end of the study visit (treatment visit five), final assessments will be conducted to review potential adverse events, concomitant medications, clinical signs and symptoms of infection, and pain status. Pain intensity of the reference ulcer will be assessed before and after any wound cleaning. If applicable, wound debridement, measurement, and photography will be performed. The study exit form will be provided to patients and additional placement of standard-of-care dressings will be provided if the wound has not healed.

Subjects will return weekly for 4 weeks after randomization unless the wound heals, the subject withdraws, or the subject is lost to follow-up.

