## 2. Materials and Methods

BLEU is a randomized double-blind controlled clinical trial comparing a synergistic antimicrobial cleanser (AMC) and an antimicrobial gel (AMG) to a normal saline wash and an amorphous gel (NSS-HG) in reducing bioburden and promoting healing in chronic lower extremity ulcers (clinicaltrials.gov #NCT05107050). This study will be conducted at up to five SerenaGroup^®^ Research Foundation centers throughout the United States with up to 60 subjects with acute or chronic non healing wounds participating. The study is anticipated to be completed within one year. The study population will be drawn from patients suffering from chronic wounds who are attending wound clinics or residing in skilled nursing facilities. Section 2.6 details the inclusion and exclusion criteria for the BLEU trial.

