### 2.3. Diagnosis

One of the challenges in conducting clinical trials in wound healing is ensuring that the wound type under study has been appropriately diagnosed. The clinical trial described here examines two ulcer types: diabetic foot (DFU) and venous leg ulcerations (VLU). The diagnosis of these two wounds is primarily clinical. DFUs occur on the plantar aspect of the foot in diabetic patients with sensory neuropathy. An objective assessment of vascular status using the ankle brachial index (ABI), the toe brachial index (TBI), or another screening test will rule out patients with significant ischemia. Venous leg ulcers develop on the medial or lateral gaiter regions of the lower extremities. Most clinical trials enroll VLU patients based on clinical signs and symptoms: lower extremity edema, hyperpigmentation of the skin, loss of hair, atrophy blanch, thickening of the nails, and lip dermatosclerosis. The venous ulcer is shallow with an irregular border. For ulcers that exhibit these signs, the diagnosis is straightforward. For ulcers suspected to be VLUs but that do not have the characteristic appearance, the investigator should consider biopsy to rule out vasculitis, cancer, or other pathology. The investigator may also wish to obtain a venous duplex scan to demonstrate venous insufficiency. In the past, VLU clinical trials mandated venous duplex procedures; however, this adds considerable cost to the trial without adding significant benefit.

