### 2.6. Subject Characteristics

Patients who suffer from acute or chronic wounds will be recruited for this study from participating wound clinics. Once patients agree to adhere to the study schedule (weekly visits and follow-up regimen) and read and sign the IRB approved Informed Consent Form, screening will be conducted to determine whether the inclusion criteria were met:The patient must be at least 18 years old, and if female of childbearing potential, must be willing to use acceptable methods of contraception (birth control pills, barriers, or abstinence);The presence of a DFU extending through the dermis or subcutaneous tissue or the presence of a full-thickness VLU;To assess the primary endpoint of the trial, the index ulcer must have been present for longer than four weeks prior to screening;A DFU size between 0.75 cm^2^ and 5 cm^2^ and a VLU size between 2.0 cm^2^ and 20.0 cm^2^ at first treatment visit;Circulation to the affected extremity is adequate, as demonstrated by a transcutaneous oxygen measurement (TCOM) or skin perfusion pressure (SPP) measurement of ≥30 mmHg, OR an ankle brachial index between 0.7 and ≤1.3 OR a toe brachial index > 0.5 within 3 months of the first screening visit.

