### 2.8. Statistical Methods

Summary statistics including mean, median, interquartile range, counts, and percentages are used to summarize demographic and treatment data collected from patients.

When determining sample size, a power of 80% is needed to detect a difference between groups of 0.35. With sample sizes of 30 patients per group, 80% power is achieved.

A chi-square test of independence will be conducted to assess endpoints concerning proportions. For the BLEU trial, the chi-square test will be used to assess the primary and secondary endpoint. The primary endpoint is to determine the relationship between the treatment and the patient, reaching a threshold of 40% PAR in four weeks. The secondary endpoint is to determine the relationship between the treatment and a reduction of bacterial load of <10^4^ CFU/g (by Fluorescence) by the fifth treatment visit. The assumptions of the chi-square test of independence must be met. These include randomly selected patients, independent treatment groups, and the use of two categorical frequency variables. The expected frequency for each group must be greater than five. A significance level of 0.05 will be used for this hypothesis test. For the primary endpoint, the null hypothesis states that the proportion is equal for both treatments, whereas the alternative hypothesis states that the proportion is not equal for both treatments. Statistical software such as R (version 4.3.1), Excel (version 365), or a TI-83 calculator (TI-83 Plus Graphing Calculator|Texas Instruments) will be used to calculate the chi-square test statistic and the *p*-value.

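### Ulcer type is controlled in neither the randomisation nor the tests, and the tests also drop the site stratum: validity is kept, but precision and protection against chance imbalance are lost

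*Protocol article*

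**What the plan says.** On allocation, section 2.7 of the protocol article states that "patients will be stratified by site and randomized using a block randomization scheme". On block size it adds: "Typically, a block randomization of four is used, with occasional blocks of two or six to prevent provider bias". The ratio is 1:1. Section 2 plans for at most five sites, "with up to 60 subjects with acute or chronic non healing wounds participating".

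On analysis, section 2.8 states: "A chi-square test of independence will be conducted to assess endpoints concerning proportions". It applies this test to the primary endpoint (reaching 40% PAR at four weeks) and to the bacterial-load endpoint. Mean PAR at four weeks is compared by a t-test. No section names site, ulcer type or baseline area as a stratum or covariate.

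Sections 2.1 and 2.3 describe a trial of two ulcer types, DFU and VLU. Their entry sizes differ: "A DFU size between 0.75 cm^2^ and 5 cm^2^ and a VLU size between 2.0 cm^2^ and 20.0 cm^2^ at first treatment visit" (section 2.6). Their background care also differs (sections 2.5 and 2.7): off-loading for DFU and multilayer compression for VLU.

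**The concern.** Two conditions with different causes, background care and size windows are put into one comparison of about 30 patients per arm. If DFU and VLU reach 40% PAR at different rates, an arm that happens to receive more of the faster type looks better for that reason alone. Site-stratified blocks do not prevent this, and the planned tests do not correct for it.

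In addition, randomising within site and then ignoring site makes a test conservative when sites differ. The sample size gives roughly the 80% power it aims for and little more, so any power that could be recovered is worth having.

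**Working it through.** **1. The plan's own figure.** Inputs from section 2.8: 30 per group, difference 0.35, two-sided 5%. The control rate is not given, so it is varied. For 0.30 against 0.65, the pooled rate is 0.475 and

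z = [0.35·√30 − 1.96·√(2·0.475·0.525)] / √(0.30·0.70 + 0.65·0.35) = (1.917 − 1.384) / 0.661 = 0.806, which gives power 0.79.

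Over control rates of 0.20 to 0.45 the power is 0.79 to 0.82. The stated 80% is reproduced, without continuity correction.

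**2. How often the arms differ in ulcer type.** The documents give no DFU/VLU mix, so the mix is an assumption. Ignoring blocks, the number K of VLUs in one arm is hypergeometric.
- With 30 VLUs among 60, SD(K) = √(30·½·½·30/59) = 1.95. The SD of the gap in share is 2·1.95/30 = 13 points.
- The probability of a gap of at least 6 patients (6/30 = 20 points) is 0.196. With 20 or 40 VLUs it is 0.170.
- A gap of at least 13 points has probability 0.41 to 0.44.

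Site blocking lowers the 20-point figure a little. Simulations of five sites with 12 patients each gave 13–14% with mixed blocks of 2, 4 and 6, and 15–16% with blocks of 4: about 15%.

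**3. What a gap does to the estimate.** If w is an arm's DFU share, its responder rate is w·r(DFU) + (1 − w)·r(VLU). With no treatment effect the arms differ by gap × [r(DFU) − r(VLU)]. For a 20-point gap:

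| Assumed rate difference between types | Shift | Share of the 0.35 target |
|---|---|---|
| 0 | 0 | 0% |
| 0.10 | 0.02 | 6% |
| 0.20 | 0.04 | 11% |
| 0.30 | 0.06 | 17% |
| 0.40 | 0.08 | 23% |

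**4. Error rates and power.** These come from 6,000 simulated trials per scenario, stratified by site only, with a 50% DFU share and a true difference of 0.35 for power. The control rates by type are assumptions.

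| Control rate DFU / VLU | Type I, chi-square, all trials | Type I when gap ≥ 20 points: chi-square / CMH by type | Power: chi-square / CMH by type |
|---|---|---|---|
| 30% / 30% | 0.054 | 0.063 / 0.056 | 0.799 / 0.789 |
| 40% / 25% | 0.054 | 0.061 / 0.047 | 0.794 / 0.791 |
| 50% / 20% | 0.055 | 0.081 / 0.038 | 0.804 / 0.836 |
| 60% / 10% | 0.051 | 0.155 / 0.050 | 0.796 / 0.910 |

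The conditional rates rest on about 800 trials each (13–14% of 6,000). Their standard error near 0.05 is therefore √(0.05·0.95/800) = 0.008. A second simulation gave 0.093 against 0.059 for the 50%/20% row. In further runs with equal rates, or rates 20 to 25 points apart, CMH by type changed power by −1.5 to +1.5 points.

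**5. Site.** With very different sites (logit SD 1.0, an assumption), the chi-square test has size 3.3–3.7% and CMH by site 4.5–5.0%. Power rises, for example from 0.654 to 0.699 and from 0.613 to 0.648. With logit SD of 0 to 0.5, the chi-square size is 0.044 to 0.055 and power changes by only −0.5 to +0.6 points.

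**6. Crossing type and site.** This makes 5 × 2 = 10 cells of about 60/10 = 6 patients. If neither factor matters, CMH over these cells has power 0.745 against 0.787 for the chi-square, a loss of about 4 points.

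**The case against.** The strongest case against is that nothing here is invalid. Ulcer type is randomised, so a reader who infers that it confounds the primary comparison, or that the false-positive rate is inflated, goes too far. Over all randomisations the plain chi-square keeps its level. That stands, and the point is one of precision and of protection in an unlucky trial.

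A reader might also infer that a serious imbalance is likely. It is not: about 85% of trials would show a gap below 20 points.

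Nor do the documents show that ulcer type is prognostic for this endpoint. They give no responder rates by type, section 2.1 sets one 40% goal for both, and PAR is already relative to baseline area. That stands too, which is why the shift is given as a range that includes zero. The site argument likewise carries weight only if sites differ widely, and section 2 places all of them in one research network.

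Finally, an analysis plan that is not shown may contain adjusted or sensitivity analyses. It may, but section 2.8 itself names the tests, hypotheses and significance level for these endpoints. The point concerns that stated choice, not something left out.

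**Conclusion.** The point holds as one of efficiency and robustness, and it should be acted on. Ulcer type is controlled at neither stage, and site is used in the randomisation but not in the tests. About 15% of trials would have a gap of 20 points or more in ulcer-type share. A 20-point gap moves the estimate by 2 to 8 points if the types differ by 10 to 40 points in responder rate. That is modest against 35 but enough to change a borderline result. Stratifying the test by ulcer type gains about 3 to 4 points of power at assumed control rates of 50% and 20%.

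The mix of types, the rates by type and the size of site differences are all assumptions. The gain from adjusting PAR for baseline area was not quantified.

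The conclusion also assumes that both types are enrolled. An exclusion criterion in section 2.6 rules out ulcers attributed to a condition other than diabetes, which read literally removes VLUs. It must be reconciled with sections 2.1 and 2.3 and with the inclusion criteria in 2.6. If only one type is enrolled, the ulcer-type part falls away.

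**What to change.** - **Primary test:** a CMH test stratified by ulcer type, with a stratified risk difference and 95% CI.
- **Site:** a sensitivity analysis stratified by site. The test should not be stratified by type crossed with site, because the sparse cells can cost about 4 points of power.
- **PAR:** ANCOVA with treatment, ulcer type, site and log baseline area in place of the t-test.
- **Randomisation, where enrolment is still open:** add ulcer type as a stratum, with small blocks. In simulation this cuts the SD of the gap in share from about 13 to about 5 points, and the chance of a 20-point gap to about zero. It belongs together with the stratified test: with this stratum added, the plain chi-square becomes conservative when types differ (size 0.043 at 50%/20% and 0.030 at 60%/10%).

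The cost is revised analysis wording, one more stratum in the randomisation list, a few more incomplete blocks, and about 1 point of power if ulcer type is not prognostic. No extra patients or measurements are needed, since ulcer type and area are recorded by the first treatment visit. R, already among the named software, can run these analyses.

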### 2.8. Statistical Methods

Summary statistics including mean, median, interquartile range, counts, and percentages are used to summarize demographic and treatment data collected from patients.

When determining sample size, a power of 80% is needed to detect a difference between groups of 0.35. With sample sizes of 30 patients per group, 80% power is achieved.

A chi-square test of independence will be conducted to assess endpoints concerning proportions. For the BLEU trial, the chi-square test will be used to assess the primary and secondary endpoint. The primary endpoint is to determine the relationship between the treatment and the patient, reaching a threshold of 40% PAR in four weeks. The secondary endpoint is to determine the relationship between the treatment and a reduction of bacterial load of <10^4^ CFU/g (by Fluorescence) by the fifth treatment visit. The assumptions of the chi-square test of independence must be met. These include randomly selected patients, independent treatment groups, and the use of two categorical frequency variables. The expected frequency for each group must be greater than five. A significance level of 0.05 will be used for this hypothesis test. For the primary endpoint, the null hypothesis states that the proportion is equal for both treatments, whereas the alternative hypothesis states that the proportion is not equal for both treatments. Statistical software such as R (version 4.3.1), Excel (version 365), or a TI-83 calculator (TI-83 Plus Graphing Calculator|Texas Instruments) will be used to calculate the chi-square test statistic and the *p*-value.

A *t*-test will be used to evaluate endpoints concerning mean differences between treatment groups. For the BLEU trial, the t-test will be used to assess the secondary endpoint. The secondary endpoint is to determine the percentage wound area reduction at four weeks. The assumptions of the t-test must be met. These include randomly selected, independent, normal variables that have similar variance. A significance level of 0.05 will be used for this hypothesis test. For these endpoints, the null hypothesis states that the mean difference between the baseline and the end of the study is equal for both treatments, whereas the alternative hypothesis states that the mean between the baseline and the end of the study is not equal for both treatments. Statistical software such as R (version 4.3.1), Excel (version 365), or a TI-83 calculator (TI-83 Plus Graphing Calculator|Texas Instruments) will be used to calculate the test statistics and the *p*-value.

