## 1. Introduction

Chronic wounds cause patient suffering, challenge clinicians, and stress health systems across the world. A new medical specialty focusing on hard-to-heal wounds has emerged to meet the increasing demand posed by millions of patients with wounds that fail to heal. As with any new field, there is limited evidence supporting the treatment regimens currently in use. In addition, clinical trials in wound healing lack standardization in endpoints and consistency in design. The goal of the wound care community is to increase the level of evidence for treatment modalities, standardize clinical trial design, and develop meaningful endpoints.

Several factors contribute to delayed healing in chronic wounds [1]. Key among them are excessive amounts of bacteria. A recent clinical trial demonstrated that more than 80% of chronic wounds harbor bacterial levels that impede wound healing [2]. Moreover, the bacteria in chronic wounds exist preferentially in a biofilm phenotype [3]. The bacteria in biofilms are resistant to antibiotics and may be protected from topical antiseptics [4]. They delay wound healing and frequently recur [5]. As a result, clinicians have adopted a biofilm-based approach in the treatment of chronic wounds that includes debridement, wound cleansing, and the use of topical antimicrobials [6]. Antiseptic cleansers and topical antimicrobials are supported by preclinical evidence [7], but there are few well powered prospective in vivo clinical trials.

In current practice, the choice of wound cleansers is based on professional experience, clinician preference, or institutional policy [7]. Unfortunately, there is sparse evidence that cleansers and topical antimicrobials reduce biofilm or promote healing in patients with chronic wounds. In order to garner greater evidence for these agents, a randomized controlled double blind clinical trial design is presented.

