### 2.1. Objectives and Endpoints

The primary objective for the BLEU clinical trial is to compare healing rates (percent area reduction, PAR) between normal saline wash and an amorphous gel (NSS-HG) to the combination of a synergistic antimicrobial cleanser (AMC) and an antimicrobial gel (AMG) in chronic lower extremity ulcers, including diabetic foot (DFU) and venous leg ulcers (VLU). The primary endpoint is PAR in 4 weeks, with a goal healing rate of 40% in 4 weeks. There is a large body of evidence that supports this rate of healing for DFUs and VLUs [10], and the FDA-sponsored Wound Care Collaborative Community (WCCC) has recommended it as a surrogate endpoint [11].

In addition, an important endpoint in antiseptic clinical trials is a reduction in bacteria. The use of point-of-care fluorescence imaging has simplified this process. Fluorescence imaging will be obtained at every visit and the reduction in bacterial bioburden will be compared between ulcers treated with NSS-HG and AMC-AMG.

Additional secondary endpoints common to most wound-healing clinical trials will be the difference in pain scores and adverse events between subjects treated with NSS-HG and AMC-AMG.

Exploratory endpoints are encouraged if they do not interfere with the primary or secondary endpoints. They contribute to the body of knowledge on chronic wounds and can improve the conduct of future trials. This study will examine host protease levels (matrixmetaloproteases 8 and 9 and neutrophil elastase) using a point-of-care lateral flow test (WOUNDCHEK PROTEASE TEST, WoundChek, Gargrave, UK). In clinical trials, the diagnostic accurately identified wounds with high levels of inflammation. In wounds with a positive test for elevated protease activity (EPA) only 10% were healed at 12 weeks [12].

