## Figures and Tables

**Table 1 life-13-01983-t001:** Schedule of events.

	SV, TV 1	TV 2	TV 3	TV 4	TV 5/EOS
Window Period	Day 0	Day 7	Day 14	Day 21	Day 28
Informed consent	√				
Documentation of onset of wound	√				
Medical history and demographics	√				
Physical exam	√				
Urine or blood pregnancy test (females of childbearing potential)	√				
Infection status	√	√	√	√	√
Assessment of pain status—PEG	√	√	√	√	√
Prior and concomitant medication review	√	√	√	√	√
Wound cleansing	√	√	√	√	√
Wound measurements/photographs	√	√	√	√	√
Adverse event review		√	√	√	√
MolecuLightTM photos (2)	√	√	√	√	√
WoundChekTM protease test	√				√

**Table 2 life-13-01983-t002:** Anticipated risks.

Study Procedure	Anticipated Risks	Risk Mitigation
Wound cleansing	Pain, bleeding, allergic reaction (e.g., rash).	Procedures to be performed by trained clinical staff
Wound measurements	None anticipated	N/A
Pain assessments	None anticipated	N/A
Wound photos	None anticipated	N/A
BIAKOS™ Antimicrobial Skin & Wound Cleanser	Allergic reaction	Procedures to be performed by trained clinical staff
BIAKŌS Antimicrobial Wound Gel	Allergic reaction	Procedures to be performed by trained clinical staff
Dressing placement	None anticipated	N/A

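### The bacterial-load endpoint has no baseline condition and no named image, so it can be scored several ways, and either all-subject scoring shrinks the treatment contrast

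*Protocol article*

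**What the plan says.** Section 2.1 states the aim in general terms: "the reduction in bacterial bioburden will be compared between ulcers treated with NSS-HG and AMC-AMG". Section 2.8 makes it a binary endpoint, "a reduction of bacterial load of <10^4^ CFU/g (by Fluorescence) by the fifth treatment visit", analysed by a chi-square test of independence at the 0.05 level.

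On the device, section 2.7 says "MolecuLight i:X detects bacteria at levels greater than >10^4^ CFU/g", so the reading is in effect positive or negative against that threshold. On timing within a visit, the same section says "The MiX procedure will be performed before and after wound cleansing". Its list of treatment-visit steps calls the second image "Post debridement fluorescence imaging", although debridement itself appears only in the last item of that list. Table 1 schedules two fluorescence photos at every visit, including the last.

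The inclusion and exclusion criteria in section 2.6 do not mention baseline fluorescence. The Introduction cites a trial in which "more than 80% of chronic wounds harbor bacterial levels that impede wound healing".

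**The concern.** Four things needed to score a subject are open or badly worded.

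- **Wording.** Read literally, the phrase describes a reduction smaller than 10^4 CFU/g, which cannot be intended. The workable meaning is a load below 10^4 CFU/g.
- **Baseline.** A wound that is negative at the first visit cannot show a reduction on this device. The text does not say whether it is a success, a failure or excluded.
- **Image.** The image before cleansing reflects carry-over from the preceding week of treatment. The image after cleansing or debridement also reflects what was removed minutes earlier. These are different questions.
- **Time.** *By* the fifth visit permits status at that visit, or any negative image up to it.

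Section 2.7 says the goal of antiseptic trials is to find products that lower wound bacteria, so this endpoint lies closest to the product's mechanism. If the choices are made after the data are seen, the result can depend on them. If all subjects are analysed without regard to baseline status, the contrast is weakened.

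**Working it through.** **1. The plan's own figure.** Section 2.8 says "a power of 80% is needed to detect a difference between groups of 0.35" and gives 30 per group. No base rates are given. With a two-sided 0.05 test, 1:1 allocation and pooled variance, control rates from 0.20 to 0.45 give power of 0.789 to 0.816 at 30 per arm. The stated 80% reproduces. For 0.25 versus 0.60:

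- mean rate 0.425; √(2 × 0.425 × 0.575) = 0.699
- z = (√30 × 0.35 − 1.96 × 0.699) / √(0.25 × 0.75 + 0.60 × 0.40) = (1.917 − 1.370) / 0.654 = 0.836
- power 0.799; exact enumeration of the uncorrected chi-square gives 0.802.

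**2. Inputs for the illustration.**

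- Share negative at baseline, f: the Introduction's figure of more than 80% implies at most about 20%, if levels that impede healing correspond to more than 10^4 CFU/g. The article does not say that they do. I use 10% and 20%.
- Clearance among baseline-positive wounds: 25% versus 60%, assumed so that the difference is 0.35.
- Baseline-negative wounds stay negative in both arms: assumed here, relaxed in step 5.
- No dropout applied; none is stated.

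**3. Effect on the difference.** With clearance p among positives, each arm's all-subject rate is f + (1 − f)p if negatives count as successes, and (1 − f)p if they count as failures. In both, the difference is (1 − f) × 0.35. This is 0.315 at f = 10% and 0.28 at f = 20%.

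**4. Effect on power (exact, uncorrected chi-square).**

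| f | Scoring | Control | Active | n per arm | Power |
|---|---|---|---|---|---|
| 0% | – | 0.25 | 0.60 | 30 | 0.802 |
| 10% | negatives = success | 0.325 | 0.640 | 30 | 0.706 |
| 10% | negatives = failure | 0.225 | 0.540 | 30 | 0.720 |
| 10% | positives only | 0.25 | 0.60 | 27 | 0.741 |
| 20% | negatives = success | 0.40 | 0.68 | 30 | 0.601 |
| 20% | negatives = failure | 0.20 | 0.48 | 30 | 0.636 |
| 20% | positives only | 0.25 | 0.60 | 24 | 0.728 |

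**5. If baseline-negative wounds can recolonise.** Keep 25% versus 60% in positives, and let 60% versus 90% of negatives stay negative. At f = 20% the all-subject rates are 0.2 × 0.60 + 0.8 × 0.25 = 0.32 and 0.2 × 0.90 + 0.8 × 0.60 = 0.66, with power 0.773. At f = 10% power is 0.787. Both exceed the positives-only analysis (0.728 and 0.741). With 80% versus 95% staying negative, the all-subject power is 0.691 at f = 20% (below 0.728) and 0.748 at f = 10% (about level with 0.741). Restriction therefore does not always win.

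**6. Stratifying instead.** In a Cochran-Mantel-Haenszel test, a stratum in which every subject succeeds adds nothing to the numerator or the variance. If negatives all stay negative, the test is then essentially the positives-only comparison. If they recolonise at different rates, the stratum adds information. In simulations of these scenarios the stratified test was level with (within about one point of) or better than both the crude and the restricted analysis.

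**The case against.** The strongest objection is that a journal article condenses the protocol, so the analysis set and the image to be scored may be fixed in a fuller document. That would excuse silence. Here, however, the article gives the threshold, time point and test, and its two descriptions of the second image disagree. What it states can be followed in several incompatible ways.

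Other objections stand and limit the point:

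- A reader might infer that wounds already below 10^4 CFU/g are counted as successes. The text does not say so; *reduction* could equally mean failure or exclusion. Only exclusion avoids the shrinkage, and exclusion is not specified.
- A reader might infer that the unnamed image also biases the comparison towards no difference. Nothing supports that. The assigned cleanser is applied between the two images, so the later one could enlarge the contrast.
- A reader might infer that the sample size is wrong. The 0.35 is not tied to the bacterial endpoint, so no stated power claim is refuted.
- Restricting to positive wounds is not a sure gain. The Introduction says biofilms often recur, and step 5 shows that restriction can then lose power and discard informative randomised subjects.
- *By* the fifth visit may simply mean the final assessment. That is a natural reading, but one word would settle it.

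**Conclusion.** The point holds in this form: the responder rule for the bacterial endpoint is badly fixed. It lacks a baseline condition, a named image and an unambiguous time point. Either all-subject scoring reduces a difference among positive wounds by the factor (1 − f) when baseline-negative wounds stay negative. At the 20% ceiling that takes 35 points to 28, with power of 0.60 to 0.64 at 30 per arm; at 10% it takes 35 to 31.5, with power of 0.71 to 0.72.

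These sizes rest on the assumed 25% and 60% clearance, on the Introduction's figure applying to this threshold, and on negatives staying negative. They illustrate scale and are not trial figures. The choice of image is a matter of analytic freedom and interpretation, with no known direction. The change should be made before any outcome data are examined.

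**What to change.** In section 2.8:

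1. Define success as a load below 10^4 CFU/g (fluorescence-negative) **at** TV5, on the image taken before cleansing and before debridement.
2. Compare arms in all randomised subjects with a test stratified by, or adjusted for, fluorescence status on the TV1 pre-cleansing image, for example Cochran-Mantel-Haenszel.
3. Report clearance among baseline-positive wounds as supportive.
4. Reconcile the naming of the second image within section 2.7 (after cleansing, or after debridement).

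Because section 2.7 ends weekly visits when the wound heals, the definition should also say how a wound healed before TV5 is scored.

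The cost is slightly more analysis work. Both images are already scheduled at TV1 and TV5, so no new data are needed and no subjects are lost.
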